### Recruitment {15}

According to the current admission rate at the Mansoura University – Isolation Hospital, the admission rate is 250 cases per month on average; our needed sample is 220 cases. We have already finished patient recruitment.

### Assignment of interventions: allocation

#### Sequence generation {16a}

A pharmacist, not involved in the study, created a randomization table (1:1) using computer-generated random permuted blocks (4, or 6 in each block).

#### Allocation concealment {16b}

The same pharmacist allocated patients to either group, without making the randomization table available to the study group. Randomization was conducted within 24 h after hospital admission after evaluation of the inclusion criteria. We started patient recruitment only after the registration of the study protocol on ClinicalTrial.gov.

Patients were randomized to receive either placebo or atorvastatin 40 mg/day orally for 28 days. All patients received the standard of care according to local hospital protocol. Antiviral treatment was allowed and reported.

#### Implementation {16c}

Randomization table was available only with the pharmacist who assigned each group for the intervention or the control.

### Assignment of interventions: blinding {17a}

Patients, caregivers, data collectors, and data analysts are blinded for the study group. The Delta Pharma company (Egypt) provided the atorvastatin and a similar placebo. The company did not—and will not—participate in any step of the study, including participant recruitment, data collection, data analysis, or results reporting. The company prepared a similar package of drug and placebo (labeled as A and B).

Even the pharmacist—involved in treatment allocation—will not know what the treatment group is, just A or B.

#### Procedure for unblinding if needed {17b}

Data Safety and Monitoring Board (DSMB) will be kept blinded for the assignment groups except if the termination of the study is an issue.

For emergency unmasking, one of the directors of Mansoura COVID-19 research council, who will not participate in the study, will have the true labels and the randomization table in a closed envelope. The envelope will be only opened if DSMB decided to unmask for a safety issue.

### Data collection and management

#### Plans for assessment and collection of outcomes {18a}

Our primary outcome, 28-day all-cause mortality, is highly objective. We ascertained mortality by a telephone call or by reviewing the national death index. Outcome assessors were trained to collect the COVID19 WHO disease progression score.

We added the definitions of the outcomes to the paper CRF to guide the outcome assessor while collecting data. Age and study durations were collected as dates (i.e., date of birth, date of admission, and date of discharge) to calculate the continuous variable on data cleaning before analysis.

Categorical outcomes were ascertained as continuous outcomes—as appropriate—and were categorized on the data analysis stage. The CRF—with the data and code dictionary—is available as a supplementary file (S3) to the protocol.

#### Plans to promote participant retention and complete follow-up {18b}

Patients started and almost received their intervention within the hospital. We educated patients and emphasized receiving their study drug after hospital discharge and contacted with telephones for follow-up. On the hospital discharge, patients received their expected doses of the assigned intervention.

#### Data management {19}

We collected the data in a paper case report form (CRF) and upload the data into an electronic CRF after 1–2 months of the patient enrolment. Paper CRF with the proposed coding was prepared **(**supplement S3), coding for missing data as 9999. Four investigators double-checked the data (2 investigators per 110 cases).

#### Confidentiality {27}

Patient confidentiality will be kept before, during, and after the study. Anonymized CRF papers were uploaded to electronic CRF. After the end of the study, the paper CRF will be kept in the hospital record room—only accessed by the research team after authorization of the IRB.

#### Plans for collection, laboratory evaluation, and storage of biological specimens for genetic or molecular analysis in this trial/future use {33}

We did not plan to keep the samples for further evaluation or future studies. Laboratory and biological specimens were manipulated according to the institution’s protocol.

### Statistical methods

#### Statistical methods for primary and secondary outcomes {20a}

The primary analysis will be based on the intention-to-treat strategy.

Categorical variables will be presented as proportion and percent. Continuous variables will be presented as mean (standard deviation) for parametric data or as a median (25th-75th percentile) for non-parametric data.

Chi-square test and *t*-test will be used to conduct a univariate analysis of demographic features correlated with study groups. We will report the 95% confidence interval and the *P*-value for our statistical tests.

In each group, we will compare the 28-day all-cause mortality rate (primary outcome) using the chi-square test with reporting the rate ratio and 95% confidence interval.

Statistical analysis will be achieved with SPSS, version 26. The level of statistical significance will be *p*-value ≤ 0.05.

#### Interim analyses {21b}

After recruitment of 25, 50, and 75% of the planned sample size, we performed interim analyses of the in-hospital mortality.

The Data Safety Monitoring Board (DSMB) and the IRB members were blinded for the study allocation. Results of the interim analysis are presented in Fig. 2. They were timely reported and revised by the IRB and the DSMB.

**Fig. 2 Fig2:**
[figure not shown]
Interim analyses of the in-hospital mortality analyzed using *χ*^2^ at 25%, 50%, and 75% of patients, reporting the percent on the *Y*-axis and the number/total within the bars

#### Methods for additional analyses (e.g., subgroup analyses) {20b}

Subgroup analysis will be conducted for the following subset which will be selected 48 hours after recruitment:Patients with and without invasive mechanical ventilationSevere cases and critically ill cases

We will run a multiple logistic regression for the association between receiving atorvastatin and 28-day all-cause mortality, controlling for age, gender, the number of comorbidities (DM, HTN, IHD, AF, COPD), and COVID19 severity (severe or critical).

A multi-linear regression model will be used to assess the reduction in ventilation duration, controlling for the same risk factors in the logistic regression model.

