### Eligibility criteria {10}

#### Inclusion criteria

We included adult patients (≥18 years old) with severe or critical COVID-19 admitted to the COVID-19 Mansoura University Isolation Hospital. We included patients who are PCR-confirmed, clinically or radiologically diagnosed with COVID-19.

Cases are defined as severe or critical according to the WHO definition [17], where severe cases have the clinical signs of severe pneumonia and SpO_2_ < 90% on room air or RR > 30 breaths/min without any critical criteria, while critical cases have ARDS, or sepsis, septic shock or pulmonary embolism, acute coronary syndrome, or acute stroke.

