#### Exclusion criteria

Exclusion criteria were chronic statin use, serum creatine kinase (CK) > 5 times the upper limit of normal (ULN), serum transaminases > 5 times ULN, acute hepatic failure, chronic liver disease (Child-Pugh Classification C), history of rhabdomyolysis or myopathies, severe renal impairment not receiving renal replacement therapy (estimated Cr cl< 30 ml/min ), pregnant and lactating women, patients who are expected to die within 48 h, or patients on chronic colchicine, cyclosporine, or ritonavir.

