### Strategies to improve adherence to interventions {11c}

Patients started the drug during hospitalization, and, on discharge, they received the estimated amount of their study drug and were educated to complete the 28-day treatment. Additionally, we contacted them by telephone (or WhatsApp) after their discharge to ensure adherence to treatment.

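### Both mortality subgroups are fixed by status 48 hours after recruitment, after randomisation, so their treatment effects can be biased; status at randomisation should be used instead.

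*Protocol article*

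**What the plan says.** Under Methods for additional analyses {20b}, the protocol article states: "Subgroup analysis will be conducted for the following subset which will be selected 48 hours after recruitment". Two splits follow: invasive mechanical ventilation or none, and severe or critical disease. The same section then gives a logistic model for 28-day mortality adjusted for age, gender, number of comorbidities and COVID-19 severity, and a linear model for ventilation duration with the same covariates. It does not say when the severity covariate is measured.

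On timing, Allocation concealment {16b} says: "Randomization was conducted within 24 h after hospital admission after evaluation of the inclusion criteria". Strategies to improve adherence {11c} says: "Patients started the drug during hospitalization"; the hour of the first dose is not given. Severity is already assessed at entry: Inclusion criteria state "Cases are defined as severe or critical according to the WHO definition".

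Secondary outcomes include the need for invasive ventilation, the WHO progression scale from day 3, and in-hospital deep vein thrombosis or pulmonary embolism. Exclusion criteria remove "patients who are expected to die within 48 h". Statistical methods {20a} says: "The primary analysis will be based on the intention-to-treat strategy".

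**The concern.** Randomisation makes the arms comparable as they stand at randomisation. A subgroup formed later keeps that comparability only if treatment has no influence on who enters it. Here the subgroup variables are ventilation and severity, which the trial itself treats as possible results of treatment. Pulmonary embolism is one of the critical criteria and also part of a secondary outcome, and the Background argues that statins act on thrombosis and on the inflammatory path to respiratory failure. By the trial's own rationale, the drug could move patients from one subgroup to the other.

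If it does, the subgroup results can mislead in two ways. A benefit that works by preventing early progression can disappear inside both subgroups, because the patients who benefited have changed group. Or, with no true effect on death, the drug can look harmful in both. Patients who die before 48 h raise a further problem. They have no 48-h status, the article gives no rule for them, and leaving them out would depart from intention to treat.

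**Working it through.** **1. Is 48 h after randomisation on every reading?** If recruitment means admission, randomisation falls between 0 and 24 h, so the 48-h point comes at least 48 − 24 = 24 h later. If recruitment means enrolment or randomisation, the gap is about 48 h. On both readings status is taken after randomisation. No section says that entry status is used for the subgroups.

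**2. The plan's own figure.** The subgroup analysis has none. The sample size is reproduced only to show that it does not depend on 48-h status. With mortality 0.6 v 0.4, two-sided alpha 0.05 (sidedness assumed) and power 80%:

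n = [1.96·√(2·0.5·0.5) + 0.842·√(0.6·0.4 + 0.4·0.6)]² / 0.2² = (1.386 + 0.583)² / 0.04 ≈ 97 per group, as stated.

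**3. Benefit acting only through 48-h status (assumed).** Control mortality is 60%, as in Sample size {14}. Assume that 50% of controls are in the worse state at 48 h, and that mortality is 85% in the worse state and 35% in the better one, in both arms.

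- Control: 0.50·0.85 + 0.50·0.35 = 0.600.
- Odds ratio of the drug on status 0.67: proportion worse = 0.67/1.67 = 0.401; mortality = 0.401·0.85 + 0.599·0.35 = 0.551.
- Odds ratio 0.52: proportion worse = 0.52/1.52 = 0.342; mortality = 0.342·0.85 + 0.658·0.35 = 0.521.

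The overall benefit is 4.9 or 7.9 percentage points. Within each 48-h subgroup the difference is 0 (odds ratio 1.00), by construction.

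**4. No true effect on death (assumed).** Let U be an unmeasured standard normal frailty, A the arm, θ the odds ratio of the drug on being in the worse state, and λ a slope:

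- logit P(worse at 48 h) = a + λU + A·log θ
- logit P(death) = c + λU

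The intercepts are set to give 60% mortality and 30% or 50% of controls in the worse state; λ is 1 or 2. Mortality in the worse state is E[P(worse)·P(death)] / E[P(worse)], averaged over U, and likewise for the better state.

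| θ | Subgroup odds ratios for death | Odds ratio adjusted for 48-h status |
|---|---|---|
| 1.0 | 1.00 | 1.00 |
| 0.8 | 1.03–1.07 | 1.03–1.06 |
| 0.67 | 1.05–1.14 | 1.05–1.12 |
| 0.5 | 1.08–1.25 | 1.08–1.21 |

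One cell in full (λ = 1, 50% worse, θ = 0.5): mortality in the worse subgroup is 0.684 on control and 0.706 on atorvastatin, so the odds ratio is (0.706/0.294)/(0.684/0.316) = 1.11. In the better subgroup it is 0.516 and 0.540, odds ratio 1.10. The true value is 1.00 in each.

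**5. Scale against sampling error.** With 55 patients per arm in a subgroup (half of 110) and mortality 0.684, the standard error of the log odds ratio is √(2/(55·0.684·0.316)) = 0.41. The 95% interval then spans a factor of e^(1.96·0.41) ≈ 2.2 each way. The null-case biases in step 4 are smaller than this.

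**6. After the fix.** Status taken at or before randomisation cannot be changed by the drug, so θ = 1. The first row of the table applies, and this selection bias is zero.

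**The case against.** The strongest reply is that the point concerns an additional analysis only. The primary comparison is an intention-to-treat chi-square test that uses no 48-h status. That stands, and it sets the grade.

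A second reply is that bias needs an early effect. The documents give no estimate of one, and the time of the first dose is not stated. That also stands: the right wording is that the subgroup effects can be biased, not that they are. The sizes in the working are illustrations, and the zero difference in step 3 is built into its assumptions.

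Third, a reader might infer that the severity-adjusted odds ratio is biased too, since its covariate carries the same two labels. The documents do not support this. The covariate appears in a separate paragraph without the 48-h qualifier, beside age, gender and comorbidities, and severe or critical is defined at inclusion. Entry severity is the natural reading, and the last column of the table applies only if 48-h severity were used. Nor would such adjustment always pull the odds ratio towards 1: in step 4 it moves away from 1, towards apparent harm.

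Fourth, excluding patients expected to die within 48 h reduces the number of early deaths. It does not remove the problem, because unexpected early deaths remain. How they would be handled is not stated, so it cannot be said that they will be dropped.

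None of this alters the timing itself: the article states the 48-h rule outright and no other section corrects it.

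**Conclusion.** The point holds for the two subgroup analyses. As written, both condition on a state reached after randomisation that the drug may change and that overlaps with the trial's secondary outcomes. Their validity rests on the drug having no effect on ventilation, severity or death in the first 48 h, which the trial cannot take for granted.

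The size is unknown: nil without an early effect, modest for a small one (subgroup odds ratios of 1.03 to 1.07 under a true null when θ is 0.8), and large enough to hide a benefit of about 5 to 8 points if the drug works wholly through early progression. These figures rest on the assumed frailty slopes, proportions in the worse state and mortality by state. The primary test and the sample size are untouched. This is a should-fix for a secondary analysis.

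**What to change.** Define both subgroups by status at or before randomisation: severity from the eligibility assessment, ventilation from the baseline record. Keep all randomised patients in them, including those who die before 48 h. State that the severity covariate in the logistic and linear models is the same baseline severity. If a 48-h split is still shown, label it descriptive and say how earlier deaths are counted.

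The text change is short, but it has two costs. Recruitment has ended and three interim analyses of in-hospital mortality have been done, so the redefinition must be dated and disclosed as a change made after those events. And severity was assessed for eligibility, but ventilation was not an eligibility item, so the investigators should confirm from the case report form that ventilation at randomisation was recorded. The sample size does not change.

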#### Secondary outcomes

A)
*Early outcomes*
Need for invasive mechanical ventilationInvasive mechanical ventilation and oxygen support duration (days)Time to clinical improvement (defined as 2-point reduction in the WHO disease ordinal progression scale [19] or discharge, whatever happens first)Serious adverse effect leading to drug discontinuationICU and hospitalization length of stay (days)CRP on days 3,7, 14, and 28SOFA score on days 3, 7, 14, and 28COVID19 WHO disease progression scale on days 3, 7, 14, and 28Incidence of acute kidney injury (AKI), defined as an increase in Scr by ≥ 0.3 mg/dl in 48 h or increase in Scr by ≥ 50% in 7 days or oliguria for ≥ 6 h [20]In-hospital deep vein thrombosis or PEMortality at hospital discharge

CRP, D-dimers, SOFA scores, WHO disease progression score, and AKI were evaluated only during the hospitalization period.B)*Late outcomes*: (will be published in a separate report)6-month all-cause mortalityLong-term outcomes of 6 months post-acute COVID19 syndrome▪ Pulmonary function tests (PFTs), high-resolution computed tomography of the chest, and incidence of cognitive impairment.▪ Health-related quality of life (anxiety or depression) and re-hospitalization rates▪ Extrapulmonary organ function (including eGFR, and ultrasonographic features of kidney, and liver)

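### The adjusted models grade baseline severity only as severe or critical and omit the entry WHO progression score, which costs the secondary analyses a modest amount of efficiency

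*Protocol article*

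**What the plan says.** All references are to the protocol article.

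- **Adjusted mortality model** (Methods for additional analyses {20b}): a multiple logistic regression of 28-day death on treatment, "controlling for age, gender, the number of comorbidities (DM, HTN, IHD, AF, COPD), and COVID19 severity (severe or critical"). The abstract calls this model pre-planned and reports its odds ratio after the unadjusted comparison.
- **Ventilation-duration model** (same section): a linear regression "controlling for the same risk factors in the logistic regression model".
- **Severity** (Inclusion criteria): severe disease is defined by respiratory signs without any critical criterion, "while critical cases have ARDS, or sepsis, septic shock or pulmonary embolism, acute coronary syndrome, or acute stroke". Ventilation is not part of either definition.
- **WHO scale** (Secondary outcomes): time to clinical improvement is "defined as 2-point reduction in the WHO disease ordinal progression scale", or discharge if that comes first. The scale is also listed as an outcome on days 3, 7, 14 and 28. Plans for assessment and collection of outcomes {18a} adds: "Outcome assessors were trained to collect the COVID19 WHO disease progression score".
- **Ventilation status** appears in {20b} only as a subgroup, among subsets "which will be selected 48 hours after recruitment".
- **Primary comparison** (Statistical methods {20a}): mortality is compared "using the chi-square test with reporting the rate ratio and 95% confidence interval", without adjustment.
- **Randomisation** (Sequence generation {16a}): permuted blocks of 4 or 6; no stratification factor is named.

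**The concern.** The critical category mixes very different levels of respiratory support. A ventilated patient with ARDS and an unventilated patient with an acute coronary syndrome get the same value. The WHO progression scale grades patients more finely, and the 2-point-reduction outcome implies that an entry value exists. The two models whose covariates the protocol fixes do not use it.

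Two things are at stake, both in secondary analyses. In the logistic model, a stronger baseline predictor would give the treatment test more power. In the duration model, ventilation at entry bears directly on days of ventilation. With no stratification factor named, covariate adjustment is the only stated protection against a chance difference between arms in entry ventilation, and the severity term removes only part of such a difference.

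**Working it through.** **1. The plan's own sample size.** Inputs from Sample size {14}: 0.6 versus 0.4, alpha 0.05 (taken as two-sided), power 80%, chi-square.

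n = [1.960·√(2·0.5·0.5) + 0.8416·√(0.6·0.4 + 0.4·0.6)]² / 0.2² = (1.386 + 0.583)² / 0.04 = 96.9, so 97 per arm. This matches the protocol. At 110 per arm the power is 0.848. These figures belong to the unadjusted test, so the choice of covariates does not change them.

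**2. Logistic model, with and without the entry score.** The documents give no score distribution and no prognostic strength, so both are assumed. Each simulation has 220 patients, with marginal mortality held at 60% and 40%.

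*Setting A* (1,500 runs per row): five entry levels with shares 45/30/10/10/5%; probability of being critical 25%, 60%, 100%, 100%, 100% by level; models include age and severity.

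| Log-odds of death per level | Power, severity term | Power, plus score | Gain (points) |
|---|---|---|---|
| 0 | 0.855 | 0.854 | about 0 |
| 0.4 | 0.873 | 0.881 | 0.8 |
| 0.7 | 0.859 | 0.885 | 2.6 |
| 1.0 | 0.891 | 0.933 | 4.2 |

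*Setting B* (3,000 runs per row): shares 35/30/15/12/8%; critical means the upper four levels; severity is the only planned covariate.

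| Log-odds of death per level | Power, severity term | Power, plus score | Gain (points) |
|---|---|---|---|
| 0.5 | 0.872 | 0.882 | 1.0 |
| 0.8 | 0.885 | 0.911 | 2.6 |
| 1.1 | 0.901 | 0.932 | 3.1 |
| 1.4 | 0.917 | 0.959 | 4.2 |

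If critical means the upper three levels in setting B, the gains are 0.8 to 2.1 points; with the upper two, 1.0 to 4.4.

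The standard error of the log odds ratio does not fall. In setting A at slope 0.7 it rises from 0.294 to 0.312, while the mean estimate moves from −0.899 to −0.986. The power gain comes from the conditional odds ratio moving away from 1 by more than the standard error grows.

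**3. Duration model, adding ventilation at entry.** Assumed: a share s of 10 to 30% ventilated at entry, a mean difference d of 3 to 8 days, residual SD 6 days, all ventilated patients critical, and 40% of the others critical. Then:

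- P(critical) = s + 0.4(1 − s), and q = s / P(critical)
- V = P(critical)·q·(1 − q), the variance of entry ventilation left after the severity term
- Fall in residual variance = V·d² / (36 + V·d²)

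| s, d | V | Fall in variance | SE ratio |
|---|---|---|---|
| 10%, 3 days | 0.0783 | 0.704/36.704 = 1.9% | 0.990 |
| 30%, 8 days | 0.1448 | 9.269/45.269 = 20.5% | 0.892 |

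Simulation over the same grid gave falls in variance of 2 to 21%, which is a reduction in standard error of about 1 to 11%.

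**4. Chance imbalance in entry ventilation.** At 110 per arm, one SD of the between-arm difference is √[2s(1 − s)/110], which is 4.0 percentage points at s = 10% and 6.2 at s = 30%. Multiplied by d, it shifts an unadjusted contrast by 0.12 days (4.0% × 3) to 0.49 days (6.2% × 8). With severity in the model, replace s(1 − s) by V: √(2·0.0783/110)·3 = 0.11 days and √(2·0.1448/110)·8 = 0.41 days. Under these assumptions the severity term removes only a small part of the exposure.

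**The case against.** The strongest case against is that this is a preference. The protocol prespecifies a short, sensible list of covariates, contradicts nothing, and leaves the treatment estimate unbiased under randomisation. A better covariate can be named for almost any model. The gain is small, and every input behind it is assumed: a slope of 1.4 per level, for instance, implies an odds ratio of exp(1.4 × 4), about 270, across the five levels. Recruitment is complete and in-hospital mortality has been examined at three interim looks, so a new covariate is an amendment made after outcome data exist.

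Much of this stands. It sets the size of the point, but it does not remove it, because the protocol itself fixes the list and one of its own outcomes requires the omitted variable.

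A reader might infer more than the document supports:

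- *The trial is underpowered or its N is wrong.* No. The primary test is the unadjusted chi-square and 97 per arm reproduces.
- *The treatment effect is biased.* No. A coarse baseline covariate in a randomised comparison loses efficiency and leaves chance imbalance uncorrected; it does not bias systematically.
- *The mortality odds ratio would be estimated more precisely.* No. Its standard error rises; the gain is in power. Precision is the right word only for the linear model.
- *Ventilated and unventilated patients share one intercept.* Only within a severity level. ARDS counts as critical, so the severity term absorbs part of the difference. The protocol also does not say whether the duration model covers all patients or only those ventilated; the calculation assumes all.
- *The entry score is certainly held.* The text lists only days 3, 7, 14 and 28, and the schedule figure and case report form are not shown. A recorded entry score is a sound inference from the improvement outcome, but it is an inference.

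**Conclusion.** The point holds as one about efficiency in the adjusted secondary models. Both carry baseline severity as two levels that do not identify ventilation at entry, and both omit an entry score that another outcome in the same protocol needs.

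For the logistic model the gain forgone is about 0 to 4 percentage points of power at 60% versus 40% mortality, and nothing if the score has no prognostic value beyond the planned terms. For the duration model it is about 1 to 11% of the standard error, the clearer case because entry ventilation feeds directly into the outcome. Both ranges rest on the assumed distributions, slopes and day differences above. The simulated models also omit some planned covariates (gender and comorbidity count in setting A, and age as well in setting B). The change is worth making because it is cheap, not because the planned models are invalid.

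**What to change.** In Methods for additional analyses {20b}, add the WHO progression score at randomisation to both the logistic and the linear model, as one linear term beside the severe/critical term. Settling on one form avoids adding analyst choice to a fixed model. Use the entry value, not the 48-hour status that defines the subgroups, because the latter is measured after treatment may have begun.

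Record this in a dated amendment before the A/B code is opened. If the code is already open, keep the planned model and report the extended one beside it as a labelled sensitivity analysis.

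The cost is one degree of freedom per model, an amendment to a pre-planned analysis, and a slightly different conditional odds ratio from the one now specified. No new data are needed if the entry score was recorded, so confirm that first against the case report form.

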### Sample size {14}

A sample size of 97 patients in each group would achieve at least 80 % power to detect a risk difference of 0.2 (20%) in the 28-day all-cause mortality (primary outcome) between the null hypothesis (both proportions are 0.6) and the alternative hypothesis (the proportion in the non-statin group would be 0.4).

Based on two large studies on chronic use of statin in hospitalized COVID patients, the adjusted OR of mortality was 0.52 and 0.67, which corresponds to a risk reduction of 17–27 % in mortality when the mortality is 60% in the control group; therefore, we used the 20% reduction in our assumption of the sample size [21, 22].

We assumed a significance level (*α*) of 0.05 and used the chi-square test of independent proportions in MedCalc software.

To compensate for the estimated loss-to-follow-up, we increased the sample size to be 110 patients in each group.

The mortality in the control group (60%) was estimated from the average mortality in January, February, and March 2021 at the Mansoura University Isolation Hospital among all hospitalized patients.

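### Ventilation days are analysed by linear regression with no rule for death, in a trial planning 60% v 40% mortality, so the estimate mixes duration with survival, in an unknown direction

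*Protocol article*

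**What the plan says.** The section Methods for additional analyses {20b} fixes the model: "A multi-linear regression model will be used to assess the reduction in ventilation duration", "controlling for the same risk factors in the logistic regression model". That logistic model contains age, gender, the number of comorbidities and severity (severe or critical).

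The outcome behind it is listed under Secondary outcomes as invasive "ventilation and oxygen support duration (days"), that is, a count of days. The need for invasive ventilation is a separate secondary outcome in the same list.

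The Sample size section plans for heavy mortality: "The mortality in the control group (60%) was estimated from the average mortality" in early 2021 at the same hospital, against 40% under the alternative. The text words the alternative as "the alternative hypothesis (the proportion in the non-statin group would be 0.4"), which conflicts with a 60% control rate. That is a separate matter. Since the stated hypothesis is that atorvastatin lowers mortality, 40% is read here as the atorvastatin arm.

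The article defines no ventilator-free days, no worst-score rule for death and no competing-event method for this outcome. The section on non-adherence and missing data offers available-data analysis or multiple imputation. A duration that ends because the patient died is observed, not missing, so that section does not cover it.

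**The concern.** A patient's ventilation days end at liberation from the ventilator or at death, and a linear model of raw days cannot tell the two apart. Because the model looks for a reduction in days, an early death on the ventilator counts as a good result. The planned arms differ by 20 percentage points in how often death stops the count, so the treatment coefficient would be non-zero even if the drug had no effect on how long anyone needs ventilation.

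The article also leaves the analysed population open. If all randomised patients are included, the never-ventilated presumably enter as 0 days. If only ventilated patients are included, the comparison conditions on something that happens after randomisation and is itself an outcome. Neither choice separates duration from survival.

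At stake is the reading of one prespecified secondary analysis. It could appear to contradict a real survival benefit, or add apparent support that comes only from the deaths.

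**Working it through.** **Inputs from the article.** Mortality 60% v 40%, two-sided α 0.05, 80% power, 97 per arm raised to 110 (Sample size). Linear regression on days (Methods for additional analyses).

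**Inputs assumed.** The article gives no ventilation durations, so mean days in deaths (D_died) and in survivors (D_surv) are varied. The drug is assumed to change mortality only, not duration within either fate. The 60% v 40% split is applied to the patients analysed.

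**1. The plan's own figure.** n = [1.960·√(2·0.5·0.5) + 0.842·√(0.6·0.4 + 0.4·0.6)]² / 0.20² = (1.386 + 0.583)² / 0.04 = 96.9, so 97 per arm. This reproduces. At 110 per arm the plan expects 0.6·110 = 66 and 0.4·110 = 44 deaths, or 110 of 220 patients.

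**2. Shift caused by mortality alone.** The mean in an arm is p·D_died + (1 − p)·D_surv. Atorvastatin minus control is (0.6 − 0.4)·(D_surv − D_died) = 0.20·(D_surv − D_died).

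The simulation columns use gamma durations (shape 2) capped at 28 days, 2,000 runs per scenario, and an unadjusted t-test in place of the adjusted regression.

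| Assumed mean days, deaths/survivors | Control | Atorvastatin | Difference (formula) | Difference (capped simulation, 110 per arm) | Significantly longer on atorvastatin, 60 / 110 ventilated per arm |
|---|---|---|---|---|---|
| 5/14 | 8.6 | 10.4 | +1.8 | +1.60 | 22% / 36% |
| 7/14 | 9.8 | 11.2 | +1.4 | +1.25 | 15% / 25% |
| 10/14 | 11.6 | 12.4 | +0.8 | +0.67 | 6% / 9% |
| 10/10 | 10.0 | 10.0 | 0 | 0.00 | 3% / 2.5% |
| 14/10 | 12.4 | 11.6 | −0.8 | −0.65 | 1% / 0.5% |

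In the last row the error runs the other way: ventilation looks significantly shorter on atorvastatin in 7% (60 per arm) and 10% (110 per arm) of runs. The level of mortality matters little and the gap matters a lot: 80% v 60% with 7/14 gave +1.23 days.

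**3. If never-ventilated patients enter as 0 days.** Suppose 80% of deaths were ventilated for a mean of 7 days (0.80·7 = 5.6 per death) and 15% of survivors for a mean of 14 (0.15·14 = 2.1 per survivor). The shift is 0.20·(2.1 − 5.6) = −0.7 days, in atorvastatin's favour. With 7/14 means, the sign changes once the ventilated share among survivors is below half the share among deaths (14·v_surv < 7·v_died).

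**4. The same scenarios on ventilator-free days to day 28, death scored 0.** Ignoring the cap, the expected difference is 0.20·(28 − D_surv): 0.20·14 = 2.8 days when D_surv is 14, and 0.20·18 = 3.6 when it is 10. The simulations gave about 2.9 to 3.7 days in favour of atorvastatin in every row. The sign no longer depends on when the deaths occur.

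**The case against.** **The direction is not established.** A reader might infer that the planned model is biased against atorvastatin, so that a life-saving drug would look harmful. The article does not support that as a fact. It needs deaths to have fewer ventilation days than survivors, and no durations are given. Equal means remove the shift, longer ventilation in deaths reverses it, and so can zeros for never-ventilated survivors. This objection stands.

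**Other outcomes.** A reader might extend the point to oxygen days, ICU and hospital stay, and time to improvement. The article lists these but names no analysis for them, and an article may leave that to a fuller document. For improvement, the definition is "Time to clinical improvement (defined as 2-point reduction in the WHO disease ordinal progression scale [19] or discharge, whatever happens first"), so death is not an early event there. The point is confined to the ventilation-duration regression.

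**Unseen documents.** A full protocol or analysis plan could say how deaths are handled. But the article itself names both the model and the scale, and that combination is unsuitable here, so this is not merely a missing detail.

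**Proportion.** The regression is an additional analysis of one secondary outcome, and 28-day mortality is reported beside it. Recruitment has ended and interim mortality results have been seen, so a new endpoint definition is more than a change of wording. Both points are fair. They limit the severity and require the change to be labelled, but they do not make the regression interpretable.

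**Conclusion.** The point holds for the linear regression of ventilation duration. As written, its treatment coefficient combines any effect on duration with the effect on survival and cannot be read as a reduction in ventilation time.

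Under the planned mortality gap, and with no true effect on duration, the spurious component is 0.20 × (mean days in survivors − mean days in deaths). That is +1.8 to −0.8 days over the assumed range among ventilated patients, and −0.7 days in the illustration with never-ventilated patients entered as 0. All the durations and ventilated shares are assumptions. The mechanism is certain, but the size and sign are not. The primary analysis is unaffected.

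**What to change.** In Methods for additional analyses, replace the linear regression with ventilator-free days to day 28 in all randomised patients. Score death by day 28 as the worst value: −1, or 0 if a tie with a survivor ventilated throughout is acceptable. Score survivors who were never ventilated as 28. Analyse by proportional-odds regression, or a rank-based method that admits covariates, with the same four covariates. Report raw ventilation days only descriptively, split by survival status, next to the mortality result.

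The costs are small:

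- The effect is no longer a simple mean number of days.
- The composite partly reflects mortality, and in the scenarios above wholly so. It should not be presented as independent evidence of shorter ventilation.
- The change comes after recruitment closed and after the interim looks at in-hospital mortality, and should be labelled so.
- It needs ventilation start and stop dates and dates of death. As examples of collected dates, the data-collection section gives "date of birth, date of admission, and date of discharge". The case report form is a supplement that is not shown, so it should be checked for the others before the change is adopted.
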